### Primary outcome

Reduction in the proportion of participants meeting criteria for an anxiety disorder assessed via a researcher blinded diagnostic interview at 5 months post-randomization.

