### Sample size

A Cochrane review reported on the efficacy of CBT for children and adolescents with anxiety disorders in the general population and found remission of anxiety diagnoses in 59% of CBT participants (*n* = 808) immediately post-intervention compared with 18% in controls (*n* = 542) [19]. Taking a conservative approach, we based our sample size on observing remission in 40% of the intervention group and 20% in the control group (odds ratio of 2.7) at 5 months post-randomization (approximates post-intervention point). In order to provide 80% power to detect this clinically meaningful difference, using a two sided test with alpha = 0.05 and accounting for 20% drop-out, we need to enrol 114 children in each arm (228 total children). This sample size will enable us to detect differences of 0.42 standard deviations (SDs) between the two groups with 80% power in the continuous secondary outcomes at 5 and 12 months (using a two-sided test with alpha = 0.05). Assuming that 10% of families opt out (based on our previous ADHD trials), 47% of those contacted are eligible, and 70% of those eligible consent to participate (based on our pilot study), we need to approach approximately 771 families in order to recruit the required sample of 228 children.

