### Data analysis

Primary analyses will follow the ‘intention to treat’ principle at the child level. To account for loss to follow-up, analysis of the primary outcome (presence of Separation, Social and/or Generalised Anxiety Disorder) and all secondary outcomes will be carried out using mixed effects regression. For each outcome, a single mixed effects model will be fitted incorporating baseline, 5 month and 12 month data, adjusted for gender (randomization stratification factor), using random effects to allow for the repeated measures within an individual. These models will fit separate random effects and error terms at each time point, and a separate fixed effect of treatment at each of the two post-randomization time points. This approach implicitly deals with missing data as it enables all participants with baseline data to be included in the analysis.

For the primary outcome and other binary outcomes, groups will be compared using mixed effects logistic regression, with results presented as odds ratios and their 95% confidence intervals [CI] at 5 and 12 months. For continuous and count data secondary outcomes, groups will be compared using linear or Poisson mixed effects regression, as appropriate, with results presented as mean differences (and 95% CIs) in outcomes at 5 and 12 months. In addition, we will repeat the analysis adjusted for baseline covariates as appropriate: for example, child sex (male, female), child age, medication use (yes/no), comorbidities (yes/no), therapist, and family socioeconomic status). For our primary outcome, whether the child meets criteria for an anxiety disorder (separation, social or generalised anxiety diagnosis) at 5 months, a sensitivity analysis will be conducted using multiple imputation to handle the missing data with analysis via logistic regression applied to the 5 month data only.

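### The primary odds ratio is subject-specific, while the objective, the design odds ratio of 2.7 and the sensitivity analysis are population-averaged, and the data hardly fix the scale of the primary figure

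*Protocol article*

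**What the plan says.** All places are in the protocol article.

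- **Primary outcome** (under the aims): "Reduction in the proportion of participants meeting criteria for an anxiety disorder", judged at 5 months by blinded interview. This is a statement about group proportions.
- **Sample size**: the trial is sized on "observing remission in 40% of the intervention group and 20% in the control group (odds ratio of 2.7") at 5 months. The next sentence reads "In order to provide 80% power to detect this clinically meaningful difference", and the result is "we need to enrol 114 children in each arm (228 total children").
- **Data analysis, primary model**: one mixed model per outcome covers baseline, 5 and 12 months, with random effects for repeated measures on a child. Random effects and error terms are to be separate at each time point. For the primary outcome, "groups will be compared using mixed effects logistic regression, with results presented as odds ratios and their 95% confidence intervals" at 5 and 12 months. The section does not call these odds ratios conditional, and it plans neither averaging over the random effects nor a risk difference.
- **Data analysis, sensitivity analysis**: multiple imputation for missing data, "with analysis via logistic regression applied to the 5 month data only". No random effect enters this model.
- **Participants** and **Inclusion/exclusion criteria**: every child must have at least one of the three anxiety disorders at entry, so the baseline value of the primary outcome is the same for all.

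**The concern.** Odds ratios are not collapsible. The treatment coefficient in a logistic model with a child-level random effect compares the odds for a given value of that effect. It lies further from 1 than the odds ratio formed from the two group proportions whenever the random-effect variance is above zero.

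Two things are at stake. First, readers will set the headline odds ratio beside the design figure of 2.7, although the two measure different things. Second, the sensitivity analysis is there to test the handling of missing data, but it also changes the estimand. A gap between the two odds ratios would arise with complete data and could be mistaken for an effect of dropout.

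A further difficulty concerns the random-effect structure. With one binary value per child per visit and a constant baseline, the data carry little information on a random-effect variance specific to 5 months. That variance sets the scale of the reported odds ratio.

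**Working it through.** **1. The design figures reproduce, on the population scale.**

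- Odds ratio: (0.4/0.6)/(0.2/0.8) = 2.67, stated as 2.7.
- Two-proportion sample size, two-sided alpha 0.05, 80% power: (1.96·√(2·0.3·0.7) + 0.8416·√(0.4·0.6 + 0.2·0.8))² / 0.2² = (1.270 + 0.532)²/0.04 ≈ 81.2, i.e. 82 per arm.
- With continuity correction: (81.2/4)·(1 + √(1 + 4/(81.2·0.2)))² ≈ 91 per arm.
- With 20% drop-out: 91/0.8 = 113.75, i.e. 114 per arm and 228 in total, as stated. Without the correction, 82/0.8 gives 103, which does not match.

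**2. The same proportions on the subject-specific scale.** For a random intercept with SD σ, the marginal proportion is p = ∫ expit(η + σz) φ(z) dz. Solve for η at p = 0.20 and p = 0.40; the conditional odds ratio is exp(η₄₀ − η₂₀). σ is an assumption, because the article gives no variance.

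| σ | latent ICC, σ²/(σ² + π²/3) | η₂₀ | η₄₀ | conditional OR |
|---|---|---|---|---|
| 0 | 0 | −1.386 | −0.405 | 2.67 |
| 0.5 | 0.07 | −1.459 | −0.429 | 2.80 |
| 1 | 0.23 | −1.650 | −0.490 | 3.19 |
| 2 | 0.55 | −2.228 | −0.668 | 4.76 |
| 3 | 0.73 | −2.929 | −0.880 | 7.76 |

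If the model codes presence of a disorder, the odds ratios invert: 1/2.67 = 0.375 marginal, against 1/4.76 = 0.21 conditional at σ = 2.

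**3. The reverse reading.** With 20% control remission, a conditional odds ratio of 2.67 corresponds to intervention remission of 36.5%, 31.8% or 28.8% at σ = 1, 2 or 3. The marginal odds ratios are then 2.30, 1.87 and 1.61.

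**4. Simulation of both analyses on the same data.** There were 150 trials per σ, with 114 per arm, 20% dropout at random, and a shared random intercept fitted to the 5- and 12-month data. The comparator was the 5-month odds ratio in children with data.

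| σ | median mixed-model OR | median marginal OR | rejection rate, mixed vs marginal |
|---|---|---|---|
| 1 | 3.00 | 2.60 | 0.79 vs 0.82 |
| 2 | 5.46 | 2.81 | 0.87 vs 0.87 |
| 3 | 8.93 | 2.75 | 0.87 vs 0.87 |

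The odds ratios separate, but the test results hardly do.

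**5. Identification with time-specific random effects.** Expected data were generated for 91 per arm from a shared intercept with σ = 1.81, 40% versus 20% at 5 months and an assumed 45% versus 25% at 12 months. The fitted model had 5- and 12-month random effects with a common SD and a free correlation ρ.

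| SD imposed | best ρ | change in log-likelihood | 5-month conditional OR |
|---|---|---|---|
| 1.81 | 1.00 | 0 | 4.4 |
| 2.5 | 0.78 | −0.0003 | 6.0 |
| 3 | 0.71 | −0.0006 | 7.8 |
| 4 | 0.63 | −0.0010 | 13.2 |

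A log-likelihood change of 0.001 cannot be detected, so the data would not choose between odds ratios of 4.4 and 13.2. The constant baseline adds nothing, and a logistic model has no free error term to estimate.

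**The case against.** The strongest reply is that nothing inferential goes wrong. The conditional odds ratio is a legitimate target, the rejection rates in step 4 are nearly equal, and no section sets a decision rule against 2.7. All of that stands. A reader might infer that the primary result is biased upward or that the trial is underpowered for it. The documents support neither: the estimand differs, and 228 is not undermined.

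The size of the gap rests on a variance that the article does not give. At σ = 0.5 the odds ratio is 2.80, close to the design value. A reader might infer that the headline figure is bound to look far larger than planned; that is conditional on σ.

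Steps 2 and 5 also use different models. The 2.8 to 7.8 range assumes a shared intercept. If each visit has its own unrelated random effect, no particular value follows, and a variance near zero (odds ratio 2.67) fits equally well. The sentence on random effects covers every outcome, and its error terms suit continuous outcomes, so it may be loose wording. That is fair, but as written it also governs the primary outcome.

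A reader might also infer that the cost-effectiveness analysis inherits the wrong effect measure. It does not: the Health economics analysis section reports mean outcomes and mean differences between groups, using generalized linear models.

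Finally, an unseen statistical analysis plan could add marginal estimates. It could, but the article itself fixes the model, the effect measure and the sensitivity analysis, and those three do not agree in scale. Direction and significance can still be compared across the two analyses; the numerical odds ratios cannot.

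**Conclusion.** The point holds as a mismatch of estimands and a weakly determined scale. The reported primary odds ratio is subject-specific, while the objective, the design figure and the sensitivity analysis are population-averaged. That the conditional odds ratio lies further from 1 holds for any random-effect variance above zero. The amount rests on an assumed shared intercept and an assumed SD, from about 2.8 (SD 0.5) to 7.8 (SD 3) against 2.67.

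The consequence is interpretive. The numerical gap between the primary and sensitivity odds ratios cannot be attributed to missing data, and with the random-effect structure as written the headline figure would depend on modelling choices. It should be settled before analysis; it does not call the trial's size or its test into question.

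**What to change.** For the binary primary outcome:

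1. Replace the time-specific random effects with a structure that the data can identify, for example one random intercept per child over 5 and 12 months.
2. Keep the likelihood-based model, which was chosen to account for loss to follow-up. Moving to standard GEE or to available-case logistic regression would give up that handling of dropout.
3. Report as the primary effect the marginal 5-month risk difference and marginal odds ratio with 95% CIs, standardised from that model by averaging over the random effect and covariates. Multiple imputation plus logistic regression, standardised in the same way, is an alternative route.
4. Use the same marginal estimand in the sensitivity analysis, so that a difference is no longer produced by a change of scale.
5. Label any mixed-model odds ratio as subject-specific and treat it as supplementary.

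The cost is a little more analysis code and a reported odds ratio closer to 1. Data collection and sample size do not change.

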### Health economics analysis

We will determine the cost-effectiveness of the Calm Kids intervention compared with usual care ‘within-trial’ from a health care perspective and a broader societal perspective. The collection of data on the Child Health Utilities Index Nine Dimension (CHU-9D) [36, 37] will enable the calculation of quality-adjusted life years (QALYs) that will form a cost-utility analysis. Health state preference values for the CHU-9D will be based on the value set derived by Ratcliffe et al., reflecting Australian adolescents’ preferences [43, 44], which will be combined with the period of the trial to derive QALYs. The cost-utility analysis will be complemented with a cost-effectiveness analysis, using the primary outcome measure of whether the child meets criteria for Separation, Social and/or Generalised Anxiety Disorder at 5 months post-randomization. This approach has been found to be useful to decision-makers [45]. Key costs and their measure (s) include: i) intervention costs: project team financial records; ii) costs accrued outside the intervention: parent-reported resource use questionnaire (baseline, 5 months and 12 months), adapted to reflect services used by children with ADHD (including community-based services, hospitalizations, out-of-pocket costs and parental productivity costs); iii) accurate and detailed health service usage for medical, pathology, diagnostic and pharmaceutical services: linked Medicare/Pharmaceutical Benefits Scheme data. Resource use and unit costs will be combined to derive a total cost for each participant. For both groups, mean values of costs and outcomes will be reported, as well as mean differences between the groups. The analyses will adopt both a health sector costing perspective (all health related costs will be included) as well as a broader partial societal perspective (parental work productivity also included). Generalized linear models will be used to assess mean difference in costs and outcomes in the two groups, using the same approach to confounding as described above. An incremental cost-effectiveness ratio (ICER) will be calculated as the difference in average cost between the groups, divided by the difference in average QALYs. Uncertainty in the data will be dealt with using nonparametric bootstrapping from the distribution of the observed cost/QALY pairs (1000 simulated replications) to determine CIs and presented in a cost-effectiveness plane along with a cost-effectiveness acceptability curve. To explore the robustness of the results, sensitivity analyses will be carried out (e.g., complete case analysis and unit cost variation).

## Discussion

The results from this study will provide evidence on whether treating comorbid anxiety in children with ADHD using a CBT approach leads to improvements in anxiety and broader functional outcomes compared with standard care. If the intervention is found to be efficacious, the evidence from this trial will inform efforts to test the translation of this intervention approach into clinical practice. We will publish our results in peer reviewed journals, present at conferences in this field and disseminate findings through professional associations (e.g., psychology, pediatrician and psychiatry associations) and ADHD organizations around the world. Eligibility for authorship will be in accordance with the Australian Code for the Responsible Conduct of Research. We also hope that our work will inform adaptations to existing clinical guidelines on the assessment and management of anxiety when it co-occurs with ADHD.

## Data Availability

Data collection is ongoing. We are collecting consent from participants for sharing de-identified data for future research. At the conclusion of the trial, requests to access the data can be made by emailing the corresponding author.

## Abbreviations

ADHD: Attention-Deficit/Hyperactivity Disorder
CBT: Cognitive-behavioral therapy
CHU-9D: Child Health Utilities Index Nine Dimension
DSM: Diagnostic and Statistical Manual of Mental Disorders
ES: Effect size
ICER: Incremental cost-effectiveness ratio
K6: Kessler 6
MCRI: Murdoch Children’s Research Institute
NAPLAN: National Assessment Program-Literacy and Numeracy
NHMRC: National Health and Medical Research Council
QALY: Quality-adjusted life years
RCT: Randomized controlled trial
SD: Standard deviation
